### Implementation strategies

Implementation strategies are interventions designed to improve the effectiveness of PATHWEIGH by promoting its adoption and use [38, 39]. These strategies were based on our development work, where key stakeholders identified the following three main areas of focus for PATHWEIGH implementation: (1) training using an e-learning module including continuing medical education (CME) credit for providers on how to counsel patients on weight loss and how to prescribe evidence-based weight loss treatments, (2) consultation support by experts in weight management built into Epic, and (3) assistance from practice facilitators available to each clinic to identify clinic champions and to assure that PATHWEIGH gets incorporated into workflows, becomes known to patients, and is monitored using quality improvement (QI) principles. All implementation strategies are deployed to clinics when they are randomly assigned to begin using PATHWEIGH. These are common resources available in other health systems to facilitate eventual dissemination.

## Evaluation

### Aim 1: Compare the effectiveness of PATHWEIGH versus standard of care (SOC) on weight loss and weight loss maintenance.

#### Outcomes and Measures

The primary outcome is patient weight between baseline and 6 months in kilograms (kg) as measured by a standard scale. The secondary outcome of weight loss maintenance will be defined at 12 and 18 months as a binary outcome of weight increase ≤ 10% from the patient’s 6-month weight. Weight outcomes will be extracted from the EMR. The primary independent variable will be the intervention status, which will be determined based on visit date and practice sequence. Additional covariate data will be collected from the EMR on potential confounders at the level of patient, provider, and practice. Patient-level data will include demographic information, health metrics, behaviors and goals, and treatment strategy employed. Provider-level data will include demographic information, years practicing, and percent time practicing. Clinic-level data will include site type/discipline, location, and size. Outcomes, measures, and timing of data collection are described in Table 3.

**Table 3 Tab3:** Summary of outcomes, measures, data sources, and timing of collection for PATHWEIGH study

Construct	Metric/measure	Method of collection	Timing

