## Aims and hypotheses

The specific aims of the current research are to:
Compare the effectiveness of PATHWEIGH versus standard of care (SOC) on weight loss and weight loss maintenance.Identify patient, provider, and clinic-level predictors that are associated with weight loss and weight loss maintenance.Describe factors associated with practice adoption, implementation, and maintenance of PATHWEIGH.

We hypothesize that PATHWEIGH will lead to greater weight loss at 6 months (primary) and greater weight loss maintenance at 12 and 18 months (secondary) compared to SOC [Hypothesis I]. Key patient, clinician, and clinic characteristics will mediate and moderate patient weight loss and weight loss maintenance [Hypothesis II]. Effective implementation will be vital to anticipated implementation and clinical outcomes [Hypothesis III].

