**Patient-specific outcomes**			
Weight-related outcomes	Weight (kg), height (cm), weight loss maintenance (weight increase ≤ 10%)	EMR	Collected during routine care
Clinical and laboratory values	Thyroid-stimulating hormone (TSH), lipid panel, liver function tests, A1c, blood pressure	EMR	Collected during routine care
Patient characteristics	Demographics (age, gender, race/ethnicity, insurance, comorbidities, medications)	EMR	Collected during routine care

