#### Analysis

A generalized linear mixed modeling strategy will be employed to account for multiple levels of correlation (i.e., between patients within practices and between measurements on a single patient over time) [44]. This approach allows for the most efficient use of data if any follow-up measurements are missing for some subjects. We will follow an intention-to-treat approach for our primary analysis, i.e., patients will be analyzed according to their clinic’s intervention condition (PATHWEIGH vs. SOC) at the time of the patient’s index visit. An index visit will be defined as the patient’s first weight-prioritized visit in an intervention condition. Follow-up visits at which weight is recorded will be associated with the intervention status of the patient’s preceding index visit.

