For the primary analysis, although the parameter of interest is weight change at 6 months, weight collected from baseline to approximately 9 months post-baseline for the individual patient will be included in the primary analysis because patients may not have visits with recorded weight within the 6-month time frame. The mixed model will include random intercepts for patient, provider, and clinic, along with fixed effects for time and intervention condition. The time effects are two-fold: (i) calendar time, divided into four 1-year periods and included as a categorical variable to flexibly model its effect on the outcome and account for temporal trends, and (ii) individual patient time, included as a continuous variable (i.e., time from baseline) to accommodate varying visit times determined by each patient’s visit schedule. The intervention condition variable will be a binary indicator that is equal to zero if the patient’s index visit occurs at a clinic when it is in the control condition and becomes equal to 1 when the patient has an index visit at a clinic after it has crossed into the intervention condition. Patient-, provider-, and practice-level covariates will be included in models if deemed to be potential confounders in univariate models. An additional fixed effect for the interaction between patient time and intervention condition will be used to estimate the parameters of primary interest, i.e., the difference in change in outcomes over time between the intervention and control conditions. The primary analysis will test the null hypothesis that the interaction effect coefficient is equal to zero to determine whether there is a significant difference in weight change between the PATHWEIGH and SOC conditions. Using the model, we will report the mean weight change in the control and intervention groups and their difference at 6 months, with corresponding 95% confidence intervals and *p* values.

To examine the secondary binary outcomes of weight maintenance (defined as < 10% weight gain at 12 and 18 months), we will use generalized linear mixed models. Since this analysis will involve a single outcome per patient, the model will only include a random intercept for provider and clinic. The test of intervention effectiveness will be captured by the fixed effect term for the intervention condition.

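### The weight loss maintenance outcome requires no weight loss and ignores baseline weight, so it does not measure retention of lost weight

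*Protocol article*

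**What the plan says.** Hypothesis I (Aims and hypotheses) expects more weight loss at 6 months and then "greater weight loss maintenance at 12 and 18 months (secondary) compared to SOC". The outcome meant to answer the second half is stated in three places in the protocol article:

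- Aim 1, Outcomes and Measures: "The secondary outcome of weight loss maintenance will be defined at 12 and 18 months as a binary outcome of weight increase", the rule in full being a "binary outcome of weight increase ≤ 10% from the patient’s 6-month weight".
- Table 3, patient-specific outcomes: "weight loss maintenance (weight increase ≤ 10" per cent, with no reference weight named.
- Aim 1, Analysis: "secondary binary outcomes of weight maintenance (defined as < 10% weight gain at 12 and 18 months", again with no reference weight named and with a strict inequality.

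None of the three asks for any loss by month 6, sets a minimum loss, or mentions baseline weight. The outcome is modelled with one value per patient and random intercepts for provider and clinic, and "The test of intervention effectiveness will be captured by the fixed effect term for the intervention condition". The primary model uses weights to about 9 months only. The Methods describe no analysis of change from baseline at 12 or 18 months, although the abstract speaks of weight loss and maintenance at 6, 12 and 18 months.

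**The concern.** Maintaining a weight loss means that a loss occurred and is still there. The stated rule asks only whether weight rose by more than 10% after month 6. A patient who never lost weight, or who gained by month 6 and stayed there, counts as a success. A patient who remains below the starting weight can count as a failure.

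The reference point is also the time point of the primary outcome. If PATHWEIGH works at month 6, its patients are judged against a lower weight and have more to regain.

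This is the only endpoint specified for the long-term half of Hypothesis I, and the moderation analyses of Aim 2 reuse the Aim 1 outcome models. A favourable result would not show that loss was sustained. A null or reversed result could be misread as PATHWEIGH failing to sustain it.

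**Working it through.** **The plan's own figures.** The protocol gives no power or expected rate for the maintenance outcome. Its primary-outcome figures reproduce. A Hussey–Hughes variance with 20/18/19 clinics, four periods, 30 patients per clinic-period and total variance 1 gives standard errors of 0.04176 (ICC 0.02) and 0.04286 (ICC 0.05). Multiplied by 1.960 + 0.842 these give 0.117 and 0.120, against the stated 0.118 and 0.121. The conversions also agree: 0.118 × 10.1 = 1.19 and 0.121 × 10.1 = 1.22 percentage points. These figures neither support nor weaken the point; they supply the SD and effect size for step 2.

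**Step 1. What the rule accepts and rejects (no assumptions).** Let *L* be the fractional loss at month 6. Success means final weight ≤ (1 − *L*) × 1.10 of baseline. Full regain counts as success when (1 − *L*) × 1.10 ≥ 1, that is, *L* ≤ 1 − 1/1.10 = 0.0909.

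| Change by month 6 | Highest final weight still a success (% of baseline) |
|---|---|
| none | 110.0 |
| −5% | 104.5 |
| −10% | 99.0 |
| −12% | 96.8 |
| −15% | 93.5 |

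Three patients:

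- Loses 5%, regains 9.9%: 0.95 × 1.099 = 1.044 of baseline. Success.
- Gains 5%, then 9% more: 1.05 × 1.09 = 1.1445 of baseline. Success.
- Loses 12%, regains 11%: 0.88 × 1.11 = 0.977 of baseline. Failure.

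The more a patient lost, the stricter the limit relative to baseline.

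**Step 2. Can the better arm score worse? (illustration under assumptions)** From the protocol: SD 10.1 for percentage change, and a benefit of 1.2 points, about the detectable difference. Assumed: mean 6-month change of −1% under SOC; regain equal to a fixed share of any loss, plus a drift of 0.5 and noise with SD 5, all in percentage points of baseline. Two million simulated patients per arm:

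| Share of loss regained | Success, SOC | Success, PATHWEIGH | Mean 12-month change, SOC | Mean 12-month change, PATHWEIGH |
|---|---|---|---|---|
| 30% | 91.7% | 90.6% | +0.88% | −0.13% |
| 50% | 86.5% | 84.6% | +1.77% | +0.92% |
| 70% | 81.3% | 78.6% | +2.69% | +1.96% |

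In each row the arm with the lower mean weight has the lower success rate. With a 3-point benefit the gap against PATHWEIGH is about 3.0, 5.3 and 7.2 points. With a 6-month SD of 6 and a 1.2-point benefit it is 0.9, 1.7 and 2.7 points. At SD 10.1, 49–55% of SOC successes had lost no weight by month 6.

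For contrast, an endpoint of at least 5% below baseline at both months 6 and 12 (an illustrative threshold, not from the documents) favours PATHWEIGH in the same three scenarios: 22.7% vs 26.2%, 18.0% vs 20.7% and 12.2% vs 14.1% (SOC vs PATHWEIGH).

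**The case against.** The protocol may define maintenance operationally as limited gain after a 6-month loss phase, and it does test that. This is a secondary outcome; the primary estimate and the sample size do not depend on it. Both points stand and bear on severity. They do not make the rule measure retained loss.

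Four stronger readings are tempting, and the documents do not support them:

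- *Almost everyone succeeds.* If 6-to-12-month change had mean +1% and SD 4 to 6, success would be Φ((10 − 1)/SD) = 98.8% to 93.3%. Those inputs are assumed. The one documented SD, 10.1, gives Φ(9/10.1) = 81%, and the protocol does not say that it applies to that interval. Nor does it report how much weight is usually lost in routine care.
- *The comparison is biased against PATHWEIGH.* This needs regain to increase with prior loss. PATHWEIGH is continuing care with encouraged follow-up (Clinician workflow), so further loss after month 6 is also compatible with the documents and would reverse the direction.
- *Patients without a 6-month weight are dropped.* The text does not say so. How that weight is obtained, and how missing values are handled, may properly sit in an analysis plan.
- *The analysis set is every index patient.* The sentence that "patients will be analyzed according to their clinic’s intervention condition (PATHWEIGH vs. SOC) at the time of the patient’s index visit" concerns the primary analysis. The set for the secondary outcome is not stated. Limiting it to patients who had lost weight would not rescue the definition, since that would select on a post-intervention result.

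**Conclusion.** The point holds as a defect of definition. The outcome records the absence of a gain above 10% after month 6, not retention of lost weight, and no other analysis in the Methods fills that gap at 12 or 18 months. This rests on the protocol's wording and on arithmetic alone: losses up to about 9.1% can be wholly regained and still succeed, and a patient at 104.4% of baseline succeeds while one at 97.7% fails.

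That the outcome can penalise the arm with more 6-month loss is conditional on regain rising with prior loss. Under the scenarios above with a 1.2-point benefit, the wrong-way gap is about 1 to 3 percentage points. The documents contain no regain data with which to judge how likely those scenarios are.

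The mismatch between at most 10% and less than 10%, and the reference weight missing from Table 3 and the Analysis section, are editorial but should be corrected together with the definition. Severity: should-fix, because the primary outcome is unaffected.

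**What to change.** Make the 12- and 18-month secondary outcome the difference between conditions in weight change from index weight, estimated from a mixed model on weights to 18 months. Patient time should enter flexibly, as categorical windows or splines, each interacting with condition. Simply running the primary model to 18 months would not do: its single continuous time-by-condition term forces a linear arm difference and cannot separate early loss from later maintenance.

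If a binary outcome is kept, define it as a pre-specified loss from index weight that is present at month 6 and still present at month 12 (or 18). Assess it among all index patients, without restriction to those who had lost weight at month 6. Handle missing weights by a model or multiple imputation, not as failures, because visit frequency may differ between conditions.

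Use one reference weight throughout, and one inequality for any binary rule, in Outcomes and Measures, Table 3 and the Analysis section.

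Cost: revised outcome wording in the protocol, the analysis plan and, where it carries the same definition, the registration, plus a modest amount of extra modelling for weights missing in routine care. No new data collection is needed, since weights are already extracted from the record every 6 months until September 2025. Enrolment began in March 2021, so the change should be dated and justified.

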**Patient-specific outcomes**			
Weight-related outcomes	Weight (kg), height (cm), weight loss maintenance (weight increase ≤ 10%)	EMR	Collected during routine care
Clinical and laboratory values	Thyroid-stimulating hormone (TSH), lipid panel, liver function tests, A1c, blood pressure	EMR	Collected during routine care
Patient characteristics	Demographics (age, gender, race/ethnicity, insurance, comorbidities, medications)	EMR	Collected during routine care
**Clinician and clinic staff-specific outcomes**			
Clinic characteristics	# and characteristics of clinicians and patients empaneled to the clinic	Survey to practice leadership	Baseline
Practice culture	Practice culture scale [40, 41]	Survey to providers and staff	Baseline and 1-year post-intervention
Implementation climate	Implementation climate scale [42, 43]	Survey to providers and staff	Baseline and 1-year post-intervention
History of practice improvement	# and type of practice improvement in the past year	Survey to providers and staff	Baseline and 1-year post-intervention
Self-efficacy and satisfaction	One item assessment of perceived confidence in ability to provide weight management, one item assessment of perceived satisfaction	Survey to providers and staff	Baseline and 1-year post-intervention
**RE-AIM Outcomes**			
**Reach** – The absolute number, proportion, and representativeness of individuals who participate	#/characteristics of patients in PATHWEIGH out of weight-prioritized and eligible per clinic	EMR	Baseline (patient characteristics) and at each 1-year step (patient participation)
	Barriers, facilitators to participation and outcomes	Interviews with selected patients	6-month post-intervention start for the patient
**Effectiveness** – The impact of an intervention on important patient outcomes	Evaluated using weight-related outcomes described above.		
**Adoption** – The absolute number, proportion, and representativeness of settings and providers who initiate the intervention	Use of PATHWEIGH by any provider in a clinic (setting level) and each provider (provider level)	Survey to practice leadership (practice characteristics), EMR (provider use of PATHWEIGH)	Baseline and at each 1-year step
	Factors influencing adoption/implementation	Interviews with selected providers and staff	Baseline and 1- year post-intervention start for each sequence
**Implementation** – The intervention agents’ fidelity to the various elements of the intervention’s protocol including consistency of delivery as intended and the time and cost of the intervention	Fidelity to PATHWEIGH functional core components and SOC in control clinics; use of implementation strategies; Clinician use of PATHWEIGH for > 50% weight-prioritized visits; e-learning module completion per clinician; use of consultation; participation in PF trainings	EMR	Ongoing collection; review at 6-month post-intervention start and study end; completion of implementation strategies
	Acceptability of PATHWEIGH; adaptations	Survey to all providers, some staff, and selected patients	6- month post-intervention start for that cohort
	Barriers, facilitators to implementation	Interviews with selected providers, clinic leaders, and staff	1-year post-intervention start for each cohort
	Cost and resources for implementation	Cost/resources interviews with practice managers and selected provider/staff by research assistant	Control condition and 1-year post-intervention start for each cohort
**Maintenance** - The extent to which the intervention becomes part of practice	Plans to continue/adapt PATHWEIGH past study	Survey and interviews with practice managers and selected providers and staff	1-year post-intervention start for each cohort; and study end

Abbreviations: *EMR* electronic medical record, *PF* practice facilitator, *SOC* standard of care

#### Analysis

A generalized linear mixed modeling strategy will be employed to account for multiple levels of correlation (i.e., between patients within practices and between measurements on a single patient over time) [44]. This approach allows for the most efficient use of data if any follow-up measurements are missing for some subjects. We will follow an intention-to-treat approach for our primary analysis, i.e., patients will be analyzed according to their clinic’s intervention condition (PATHWEIGH vs. SOC) at the time of the patient’s index visit. An index visit will be defined as the patient’s first weight-prioritized visit in an intervention condition. Follow-up visits at which weight is recorded will be associated with the intervention status of the patient’s preceding index visit.

For the primary analysis, although the parameter of interest is weight change at 6 months, weight collected from baseline to approximately 9 months post-baseline for the individual patient will be included in the primary analysis because patients may not have visits with recorded weight within the 6-month time frame. The mixed model will include random intercepts for patient, provider, and clinic, along with fixed effects for time and intervention condition. The time effects are two-fold: (i) calendar time, divided into four 1-year periods and included as a categorical variable to flexibly model its effect on the outcome and account for temporal trends, and (ii) individual patient time, included as a continuous variable (i.e., time from baseline) to accommodate varying visit times determined by each patient’s visit schedule. The intervention condition variable will be a binary indicator that is equal to zero if the patient’s index visit occurs at a clinic when it is in the control condition and becomes equal to 1 when the patient has an index visit at a clinic after it has crossed into the intervention condition. Patient-, provider-, and practice-level covariates will be included in models if deemed to be potential confounders in univariate models. An additional fixed effect for the interaction between patient time and intervention condition will be used to estimate the parameters of primary interest, i.e., the difference in change in outcomes over time between the intervention and control conditions. The primary analysis will test the null hypothesis that the interaction effect coefficient is equal to zero to determine whether there is a significant difference in weight change between the PATHWEIGH and SOC conditions. Using the model, we will report the mean weight change in the control and intervention groups and their difference at 6 months, with corresponding 95% confidence intervals and *p* values.

To examine the secondary binary outcomes of weight maintenance (defined as < 10% weight gain at 12 and 18 months), we will use generalized linear mixed models. Since this analysis will involve a single outcome per patient, the model will only include a random intercept for provider and clinic. The test of intervention effectiveness will be captured by the fixed effect term for the intervention condition.

The primary analysis is expected to provide a conservative estimate of the treatment effect, and we propose the following secondary analyses to assess the treatment effect in alternative cohorts. We will perform a per-protocol analysis that uses the described models to compare those that received PATHWEIGH to those with a SOC weight-prioritized visit. This analysis will provide a better estimate of the efficacy of the intervention by including only those in the PATHWEIGH condition that were considered to satisfy the criteria for receiving the intervention as assessed by the provider’s use of at least one of a weight prioritized visit “type”, the patient weight management questionnaire, and/or the weight management SmartSet. Additionally, we will perform an analysis using all those that are eligible for PATHWEIGH based on the criteria of age and BMI, regardless of whether they had a weight-prioritized visit. This analysis will allow us to account for the potential selection bias induced by the implementation of PATHWEIGH potentially increasing the number of weight-prioritized visits and thus increasing the enrollment of patients in the intervention period that differ systematically from those in the control period.

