#### Clinician workflow

To optimize efficiency and guide care, health care providers are encouraged to use the PATHWEIGH weight management SmartSet in Epic. A SmartSet is a documentation template used in the ambulatory setting comprised of a group of orders and other elements, such as notes, chief complaints, medications, and levels of service charges, that are commonly used together to document a specific type of visit. This SmartSet addresses the following.
Diagnosing overweight or obese patients with a BMI > 25 kg/m^2^ or > 30 kg/m^2^, respectively, recognizing these as bona fide disease states [6]Linking diagnoses for weight-related comorbidities to facilitate reimbursementPre-populating information from the patient weight management questionnaire to serve as documentation and to guide the clinician-patient discussion, and flagging weight management strategies based on guidelines from the Obesity Society [32], specifically, the discussion of lifestyle change for patients with BMI ≥ 25 kg/m^2^, consideration of medications impacting obesity as well as anti-obesity medication at BMI ≥ 30 kg/m^2^ (or BMI ≥ 27 kg/m^2^ with weight-related comorbidities) and consideration of bariatric surgery for BMI ≥ 40 kg/m^2^ (or BMI ≥35 kg/m^2^ with weight-related comorbidities)Providing options for orders that include laboratory testing, referrals, or procedures

Behavioral health professionals work alongside many of the primary care providers and are encouraged adjuncts to facilitate weight loss. Use of the PATHWEIGH tools is entirely optional for clinicians. Use may be deployed by the clinicians in advance of the visit or if they or the patient spontaneously decides to prioritize weight management. The process strongly encourages regular follow-up (usually at 4–6 week intervals and more often initially). A key advantage is that the clinician is the patient’s regular provider and will have an ongoing relationship with the patient over time and can safely manage or discontinue medications or other issues for weight-related comorbidities.

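### Weight-loss maintenance exists only for patients weighed near month 6 and again near month 12 or 18, and the plan's answer to sparse 6-month weights covers the primary outcome only

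*Protocol article*

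**What the plan says.** Under Aim 1, Outcomes and Measures, the protocol article makes maintenance at 12 and 18 months a "binary outcome of weight increase ≤ 10% from the patient’s 6-month weight". On the source of the data it says: "Weight outcomes will be extracted from the EMR". Table 3 adds that weights are collected in routine care, and the article describes no scheduled study weigh-in.

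Under Aim 1, Analysis, the primary outcome is handled longitudinally. The stated reason is that "patients may not have visits with recorded weight within the 6-month time frame". The stated response is that "weight collected from baseline to approximately 9 months post-baseline for the individual patient will be included in the primary analysis", with patient time entered as a continuous variable.

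The next paragraph turns to maintenance, restated as "defined as < 10% weight gain at 12 and 18 months". The model is fixed there: "Since this analysis will involve a single outcome per patient, the model will only include a random intercept for provider and clinic".

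The Clinician workflow section says of the intervention: "The process strongly encourages regular follow-up (usually at 4–6 week intervals and more often initially". The section on current standard of care describes no matching encouragement.

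**The concern.** Each maintenance endpoint needs two recorded weights, one near month 6 as the reference and one near month 12 (or near month 18). A patient without either one has no value. The general remark in the Analysis section, that mixed models use incomplete follow-up efficiently, is true of repeated measurements. It does not rescue a single derived value that does not exist. The plan therefore identifies the sparse 6-month weight as a problem, works around it for the primary outcome, and then makes that same weight the required reference for the secondary one.

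The comparison at 12 and 18 months is thus conditional on having returned at the right times. Return may depend on how the patient's weight is going, and one condition actively promotes return. If the two conditions select maintainers and regainers differently, a difference in maintenance can appear, or be hidden, with no difference in the underlying weight courses. Maintenance at 12 and 18 months is the secondary half of Hypothesis I, so the result will be read as evidence on durability.

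**Working it through.** **The plan's own figure.** The Sample size section gives a detectable standardized effect of 0.118 (ICC 0.02) to 0.121 (ICC 0.05) for weight change, and nothing for maintenance. I checked it with the Hussey-Hughes variance, total variance 1.
- Inputs: I = 57 clinics (20/18/19), T = 4 periods, 30 patients per clinic-period.
- U = 20×3 + 18×2 + 19×1 = 115; W = 20² + 38² + 57² = 5093; V = 20×9 + 18×4 + 19×1 = 271.
- s² = (1 − ICC)/30; t² = ICC.
- var = I·s²(s² + T·t²) / [(IU − W)s² + (U² + ITU − TW − IV)t²], where IU − W = 1462 and the second bracket is 3626.
- Detectable effect = (1.960 + 0.842)·√var = 0.117 (ICC 0.02) and 0.120 (ICC 0.05).

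This agrees with the plan to within 1%. The calculation uses all 6840 patients (57 × 120), with no allowance for missing weights.

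**Loss of patients (assumed rates).** If each of the two weights is present independently for 80, 70, 60 or 50% of patients, the pair exists for 0.8² = 64%, 0.7² = 49%, 0.6² = 36% or 0.5² = 25%. As a rough guide to precision, putting 30 × 0.6 = 18 patients per clinic-period (60% evaluable) into the formula above raises the detectable effect to 0.147–0.152. At 25% evaluable it is 0.216–0.225.

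**Bias (assumed rates).** Let p be true maintenance, a the probability that a maintainer has both weights, and b the same probability for a regainer. Then

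P(maintained | evaluable) = p·a / [p·a + (1 − p)·b].

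The observed odds are [p/(1 − p)]·(a/b). With equal true maintenance, the observed odds ratio is therefore (a/b under PATHWEIGH) ÷ (a/b under SOC), whatever the value of p. With p = 0.90 in both conditions:

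| SOC a, b | PATHWEIGH a, b | SOC observed | PATHWEIGH observed | Odds ratio |
|---|---|---|---|---|
| 0.50, 0.40 | 0.60, 0.60 | 0.45/0.49 = 91.8% | 0.54/0.60 = 90.0% | 1.00/1.25 = 0.80 |
| 0.50, 0.40 | 0.60, 0.48 | 0.45/0.49 = 91.8% | 0.54/0.588 = 91.8% | 1.25/1.25 = 1.00 |
| 0.50, 0.50 | 0.70, 0.50 | 0.45/0.50 = 90.0% | 0.63/0.68 = 92.6% | 1.40/1.00 = 1.40 |

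The middle row matters. Attendance is higher under PATHWEIGH for both groups, yet there is no bias, because the ratio a/b is the same.

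**Exposure of SOC follow-up to crossover.** Assume one-year steps and even recruitment. Control clinic-years number 20×1 + 18×2 + 19×3 = 113.
- Index visits whose month 12 precedes the switch: 18×1 + 19×2 = 56 (50%).
- Index visits whose month 18 precedes the switch: 18×0.5 + 19×1.5 = 37.5 (33%).

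So about two thirds of SOC 18-month weights fall due when PATHWEIGH is already on. The Analysis section ties follow-up weights to the preceding index visit. On that rule, a SOC patient with a weight-prioritized visit after crossover is re-indexed, and later weights count as PATHWEIGH. This is a second route by which the intervention can shape who supplies SOC maintenance data.

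**The case against.** The strongest reply is that the article fixes the reference weight, the binary form and the model, but not how the landmark weights are obtained. Windows, nearest-weight rules or imputation could use the patient's other weights, and they may well be in a statistical analysis plan that is not shown. That stands, and their absence here is not a fault. What remains is what the article does state: a longitudinal workaround for the primary outcome, followed by a single-value model for maintenance that has no such feature.

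A second reply is that weights may come from any visit at which weight is recorded, and data are taken on all encounters at the 57 clinics. Ordinary primary-care visits feed both conditions and would dilute any attendance difference. PATHWEIGH use is also optional for clinicians. Both points are fair, and they limit the likely size of the problem.

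Three stronger readings are tempting and not supported.
- A reader might infer that the plan concedes that many patients lack the weights. It says only that they may not have one, gives no share, and says this of the 6-month time frame, not of months 12 or 18.
- A reader might take it as fact that PATHWEIGH changes who returns. That is an inference from the encouragement of follow-up; the article reports no attendance data.
- A reader might expect the bias to run against PATHWEIGH. The direction depends on rates that the documents do not give.

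Nor does an endpoint need all three weights. Each needs month 6 and its own later weight.

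The analysis of all patients eligible by age and BMI does not answer the point. It addresses who enters the cohort, and it still needs recorded weights.

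**Conclusion.** The concern holds in a limited form. As defined and modelled, each maintenance endpoint rests on patients with a suitable pair of routine-care weights. The maintenance model discards the other recorded weights that the primary analysis would use, and the evaluable set may differ between conditions.

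Bias on the odds-ratio scale arises only if the maintainer-to-regainer observation ratio differs between PATHWEIGH and SOC. Its size and direction cannot be computed from the documents. The range of about 0.8 to 1.4, with 1.0 when the ratios agree, rests wholly on assumed observation rates and on equal true maintenance of 90%.

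The primary 6-month analysis is not affected. The change is worth making because maintenance is a stated hypothesis and the remedy is cheap. The documents do not show that the binary outcome must be abandoned.

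**What to change.** 1. Keep the binary outcome as defined, and report for each endpoint the number and percentage evaluable by condition. Reconcile the threshold, which includes exactly 10% under Outcomes and Measures and excludes it under Analysis.
2. Add a prespecified longitudinal mixed model of all recorded weights from baseline through about month 18, and later where available. Model patient time flexibly, allow it to differ by condition and by calendar period, and keep the patient, provider and clinic random intercepts of the primary model. Test the between-condition difference in modelled weight change from month 6 to month 12 and from month 6 to month 18.
3. Read the two results side by side. If they disagree, the evaluable percentages help the reader judge whether selection by return could explain it.

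The cost is some analysis wording and one further model, with no new data. The model targets a mean change, not a proportion, so it is a companion to the binary outcome and not a substitute. It still assumes that weights are missing at random given the recorded ones, so it lessens the selection problem without removing it. It will also have little data beyond month 18 for patients indexed last: four one-year periods counted from 17 March 2020 end in March 2024, and 18 months later is the September 2025 end of extraction.
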